#### Adverse reactions of acupuncture and countermeasures

2.8.2

Acupuncture may cause acupuncture syncope, convulsion, severe pain, stuck needle, broken needle, local infection and subcutaneous hematoma and other adverse reactions. However, they are generally mild reactions, and the prognosis is generally good after corresponding treatment.^[24]^ According to the causes of adverse reactions and the degree of adverse reactions, symptomatic treatment can be carried out, such as: detailed medical history to avoid convulsion, appropriate psychological counseling to avoid fainting, standardized needle application, auxiliary manipulation to avoid needle sticking, pain, broken needle, etc. If there are serious adverse reactions, they should be reported to the principal investigator immediately, and the details of adverse reactions should be recorded in the patient's log, and medical intervention should be carried out. If the subject or researcher thinks that the patient cannot tolerate these adverse reactions, the trial can be terminated and the subject will withdraw from the study.

### Primary outcomes

2.9

NIHSS, score, and simplified fulg Meyer (FMA) score were evaluated before treatment and on day 10. The modified Barthel Index (MBI) was evaluated before and 10 days after treatment and 30 days after treatment

### Secondary outcomes

2.10

Cortical excitability was evaluated on the day of admission and the 10th day of treatment. The patients’ mood, sleep, and diet were followed up through the treatment log. All adverse reactions and causes of shedding will be recorded in case report form (CRF) in time.

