### Ethics

2.2

This study has passed the ethics committee Shaanxi Provincial Hospital of traditional Chinese medicine ((2019)(32)), and registered on October 5, 2019 at http://www.chictr.org.cn/index.aspx, ID is chictr19000026890. Informed consent has included all the subjects involved. Any modification of the study protocol or informed consent, which may affect the rights and interests of the participants or the implementation of the study, should be reported to the Ethics Committee for approval again. If there are any serious adverse events in the trial, the ethics committee should review it in time and put forward written suggestions for modification, including sufficient power to suspend the trial.

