#### Withdrawal criteria

2.3.3

1.After inclusion, it was found that they were not suitable to continue to participate in the study.2.Those who fail to treat according to the regulations affect the evaluation of curative effect.3.Withdrawal of consent by the subject or a legal representative.4.Loss to follow-up.5.Serious adverse events.6.Significant errors or deviations were found in the clinical protocol.7.New infarct or secondary hemorrhage occurred and the condition deteriorated.

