#### Adverse reactions and countermeasures of magnetic stimulation

2.8.1

Magnetic stimulation may induce epilepsy, local skin numbness, pain and discomfort, and other adverse reactions. In the treatment process, the intensity, frequency, and stimulation times can be changed according to the patient's condition to reduce the occurrence of adverse reactions.^[21–23]^ During the study, a patient treatment log will be established to monitor all adverse reactions during treatment and follow-up, and appropriate intervention will be carried out. If serious adverse reactions occur during the treatment, they should be reported to the principal investigator immediately, and the details should be recorded in the patient's treatment log and corresponding treatment measures should be taken, such as adjusting the coil position and stimulation intensity to avoid stimulating the sensitive orbitofrontal cortex (100% RMT → 80% RMT), or giving appropriate medical intervention according to the patient's condition. If the subject or researcher thinks that the patient cannot tolerate these adverse reactions, the trial can be terminated and the subject will withdraw from the study.

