#### Safety evaluation

2.13.3

Adverse events recorded in the patient log will be analyzed as multiple variables. The number and percentage of AE patients were calculated and compared by *χ*^2^ test.

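### Collection and reporting are worded for adverse reactions, but review and analysis for adverse events, and the named data sources differ, so some serious events may be missing from the between-arm comparison

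*Protocol article*

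**What the plan says.** Five parts of the protocol article bear on how safety data are collected, escalated and analysed.

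- **Collection.** Section 2.8.1 (magnetic stimulation) states that "a patient treatment log will be established to monitor all adverse reactions during treatment and follow-up". Section 2.10 adds: "All adverse reactions and causes of shedding will be recorded in case report form (CRF) in time". The abstract also speaks of adverse reactions.
- **Reporting to the principal investigator.** Section 2.8.1: "If serious adverse reactions occur during the treatment, they should be reported to the principal investigator immediately". Section 2.8.2 (acupuncture): "If there are serious adverse reactions, they should be reported to the principal investigator immediately".
- **Ethics review.** Section 2.2: "If there are any serious adverse events in the trial, the ethics committee should review it in time". The committee's powers include suspending the trial.
- **Withdrawal.** Section 2.3.3 lists "Serious adverse events" as item 5 and, as a separate item 7, "New infarct or secondary hemorrhage occurred and the condition deteriorated". Section 2.14 also requires withdrawals and their reasons to be recorded throughout treatment and follow-up.
- **Analysis.** Section 2.13.3: "Adverse events recorded in the patient log will be analyzed as multiple variables". The number and percentage of patients with AEs are then compared by a chi-square test.

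The trial is open (section 2.12), with 21 patients per arm (section 2.5).

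**The concern.** In safety work, an adverse reaction ordinarily means an event with a suspected link to treatment, whereas an adverse event carries no such condition. A plan that collects the first and analyses the second leaves it unclear whether an event put down to the underlying stroke enters the safety table.

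That matters here for two reasons. Patients are enrolled within a month of an ischaemic stroke, so the gravest events, such as a new infarct or a haemorrhage, are also the easiest to attribute to the disease. And the treating staff know the arm. If someone must decide whether an event is a reaction before it is entered, that decision can differ between arms, and no later analysis can recover what was not entered. The abstract's conclusion expects to show that the new treatment is safer as well as more efficient, so the safety comparison carries weight.

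**Working it through.** The plan gives no figure to reproduce on this point. The check sets the sections side by side and then sizes the effect of one omitted patient.

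**1. Which term each rule uses**

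| Step | Section | Term |
|---|---|---|
| Entry in the treatment log | 2.8.1 | reactions |
| Entry in the CRF | 2.10 | reactions, plus causes of dropout |
| Report to principal investigator | 2.8.1, 2.8.2 | serious reactions |
| Ethics review | 2.2 | serious events |
| Analysis | 2.13.3 | events |

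Neither term is defined. Sections 2.8.1 and 2.8.2 open by describing reactions as things the stimulation or the needling can bring about, and every example given is an effect of the intervention. New infarct and haemorrhage are in neither list; they appear only in section 2.3.3.

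**2. Which record each rule uses**

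Section 2.10 sends reactions and causes of dropout to the CRF. Section 2.8.1 sends reactions to the log. Section 2.13.3 names the log as its source and does not mention the CRF.

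**3. Following one event through the rules**

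Take a secondary haemorrhage with deterioration that staff attribute to the index stroke.

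- Section 2.3.3, item 7: the patient is withdrawn.
- Sections 2.10 and 2.14: the reason is recorded, and as a cause of dropout it goes to the CRF.
- Section 2.8.1: the log entry is required if the event is regarded as a reaction. If it is not, no stated rule puts it in the log.
- Section 2.13.3: the analysis uses events in the log, so this patient may not be counted.
- Sections 2.8.1 and 2.8.2: immediate report to the principal investigator is triggered by a serious reaction. Section 2.2 nevertheless calls for review of any serious event.

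**4. Whether the rules match between arms**

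The instruction to log all reactions through follow-up stands under magnetic stimulation. The acupuncture section mentions the log only in connection with serious reactions. The report to the principal investigator is tied to the treatment period in section 2.8.1 and has no time limit in section 2.8.2. Section 2.10 does cover all reactions in both arms, but through the CRF.

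**5. Size**

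Input: 21 patients per arm (section 2.5), all kept in the denominator. For *k* patients whose only AE is omitted, the shift in that arm's AE percentage is *k*/21:

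- *k* = 1: 1/21 = 4.8 points
- *k* = 2: 2/21 = 9.5 points

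The values of *k* are assumptions, because the article gives no rate for such events. A patient who also has another AE in the log is already counted, and for that patient the shift is zero.

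**The case against.** The best case on the other side is that this is loose wording in a condensed article. The parent heading of sections 2.8.1 and 2.8.2 speaks of observing adverse events, so reaction and event may be meant as synonyms. Section 2.13.3 describes the log as holding events, and section 2.10 shows that the log also follows mood, sleep and diet, so it is not confined to treatment effects. No causality assessment is described anywhere. Items 5 and 7 of the withdrawal list can overlap, so listing a new infarct separately does not mean that it is not a serious adverse event. How log and CRF are merged may be settled in a fuller document.

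Much of this stands, and it limits the point. Three stronger readings are tempting, and the article does not support them:

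- *That such events never reach the ethics committee.* Section 2.2 covers any serious adverse event, with no condition on cause.
- *That only events judged related are collected.* The terms are undefined, so that is an inference. Serious events and new infarct or haemorrhage are named in section 2.3.3, and sections 2.10 and 2.14 require withdrawal reasons to be recorded.
- *That the analysis excludes the CRF.* Section 2.13.3 names the log; it does not say the log alone.

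What the objection does not remove is that the article itself names reactions for collection, events for analysis, the CRF for dropout causes and the log for the comparison. These are statements that disagree, not details left out for brevity.

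**Conclusion.** The point holds as an inconsistency of term, data source and reporting trigger. If the rules are followed literally, an item 7 event that is not regarded as a treatment reaction is recorded, yet may be absent from the AE comparison. Because the trial is open, such omissions could differ by arm, so the AE percentages can be biased; the article does not show that they will be.

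Each omitted patient would move an arm's percentage by 4.8 points, assuming that 21 remain in the denominator and that the patient has no other logged AE. How many such events will occur is unknown. This is an inexpensive improvement worth making, not a fault that undermines the design.

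**What to change.** 1. In sections 2.8.1, 2.8.2 and 2.10, replace adverse reactions with *adverse events, whatever the suspected cause*. Apply the same collection rule to both arms and through follow-up. Record relatedness in a separate field.
2. State that every event under section 2.3.3, item 5 or 7, is also counted as an AE.
3. Have section 2.13.3 analyse AEs from the log and the CRF together, for all randomised patients.
4. Reconcile the reporting trigger in sections 2.8.1 and 2.8.2, worded for serious reactions, with the review in section 2.2, worded for any serious event, so that the two describe one route.

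The cost is a change of wording, one more field on an existing form and slightly more event recording. No treatment or sample size changes.

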### Estimation of sample size

2.11

This study is a preliminary clinical study to evaluate the efficacy and mechanism of targeted therapy before, after and during the follow-up period. We plan to enroll 42 participants in this study. (In this study, NIHSS score was used as the effect value. According to the sample size formula of good and bad clinical trials: N = 2δ^2^ × f(α,β)/(u_1_−u_2_)^2^. In the acupuncture group, the NIHSS mean value before treatment was 8.95, the standard deviation was 1.93, and the average NIHSS after treatment was 6.90, sou_1_ = 8.95, u_2_ = 6.90, δ = 1.93, α = 0.05, β = 0.1, f (α, β) = 10.5 from the table, which was substituted into the formula to calculate the sample size n ≈ 19 cases. Considering the loss rate of 10%, the total sample size required was 19 × 2 × (1 + 10%) ≈ 42 cases.)

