#### Primary outcomes

2.13.1

NIHSS score and simplified fulg Meyer score were evaluated before and 10 days after treatment, and the data were analyzed by rank sum test or *χ*^2^ test. The modified Barthel index was evaluated before and 10 days after treatment and 30 days after treatment. The data were analyzed by rank sum test or *χ*^2^ test. The statistical significance between groups will show that there are differences in modified Barthel index, NIHSS score, and simplified fulg Meyer among groups after intervention.

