## Discussion

3

Limb dysfunction after stroke is the main complication of stroke and the main cause of adult disability, which seriously affects the working ability and quality of life of stroke patients, and brings serious economic burden to patients and society. With the progress of medical technology, patients have higher expectations of limb function recovery after stroke. Therefore, we designed the clinical research program, hoping to obtain high-quality research data through the improvement of patients’ symptoms and the scale, so as to provide reliable basis for future multicenter research. As a traditional Chinese rehabilitation therapy, acupuncture and moxibustion is widely recognized in the clinical treatment and rehabilitation of stroke. Therefore, we chose the acupuncture program with high public reliability as the control group. PC6 and SP6, as the experimental group, can activate the brain area, increase the link between the brain regions, and strengthen the information exchange between the brain regions. Compared with acupuncture and moxibustion, magnetic stimulation has the advantages of noninvasive, painless, and statistical. In previous clinical trials, it has been confirmed that low-frequency rTMS is of positive significance for the recovery of motor function of stroke patients.^[25]^ However, the use of acupoint magnetic stimulation in the treatment of limb motor dysfunction after stroke is often seen in case reports, and there is no systematic theoretical guidance. The closed-loop rehabilitation theory of “center peripheral center” has great enlightenment on how to improve the treatment effect of limb dysfunction after stroke, but there are few clinical curative effect observation with high confidence based on the “center peripheral center” closed-loop rehabilitation theory. Therefore, based on this theory, we plan to give magnetic stimulation combined with peripheral magnetic stimulation at PC6 and SP6 in central M1 area to observe the effect and difference of acupuncture group on limb function after stroke.

Our scheme is only a pilot study, and its shortcomings include: small sample size, no blindness, short observation time, etc. In the experiment, we will try our best to reduce the error which may affect the research results. Finally, we will prove that rTMS combined with magnetic stimulation of PC6 andSP6 is an effective treatment for limb dysfunction after stroke.

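### The sample size enters the acupuncture group's own before-after NIHSS change (2.05 points) as the between-group difference, so the 90% power implied by β = 0.1 is not power for the trial's comparison

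*Protocol article*

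**What the plan says.** Section 2.11 bases the calculation on one of the three primary scales: "In this study, NIHSS score was used as the effect value". The formula is twice the variance times f(α,β), divided by the squared difference of two means.

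The inputs are identified openly. "In the acupuncture group, the NIHSS mean value before treatment was 8.95, the standard deviation was 1.93"; then "the average NIHSS after treatment was 6.90". These become u1 and u2, with 1.93 as the standard deviation. The error rates are "α = 0.05, β = 0.1, f (α, β) = 10.5 from the table". The result is 19 per group, doubled and raised by 10% for losses to 42.

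The comparison to be tested is set out elsewhere. Sections 2.1 and 2.5 randomise 1:1, 21 per group, to magnetic stimulation or acupuncture. Section 2.13.1 draws its conclusion between the groups after intervention: "The statistical significance between groups will show that there are differences" in the three scales. The Discussion adds "Our scheme is only a pilot study".

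**The concern.** In this formula u1 and u2 have to be the outcome means expected in the two arms. Here they are one arm's means at two times. Their difference reflects whatever made acupuncture patients improve: acupuncture, basic treatment and spontaneous recovery early after a stroke. The experimental arm also receives basic treatment and also recovers spontaneously, so the acupuncture group's change carries no information on how far the two arms will differ.

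The quantity sized is therefore not the quantity tested. A reader who sees α = 0.05 and β = 0.1 will take it that the trial has 90% power for its comparison with acupuncture. That holds only for one large between-group difference, which the protocol neither states nor justifies. The reader needs to know this when interpreting the result, particularly a non-significant one.

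**Working it through.** **Inputs (section 2.11).** u1 = 8.95; u2 = 6.90; SD = 1.93; α = 0.05; β = 0.1; f = 10.5; loss 10%. Section 2.13 makes the tests two-sided, which agrees with f: (1.960 + 1.2816)² = 10.51.

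**Reproducing the plan's figure.**
- Difference: 8.95 − 6.90 = 2.05 points, which is 2.05 / 1.93 = 1.06 SD.
- Per group: 2 × 1.93² × 10.5 / 2.05² = 2 × 3.7249 × 10.5 / 4.2025 = 18.6, so 19.
- Total: 19 × 2 × 1.1 = 41.8, so 42.

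Both figures reproduce.

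**What 2.05 would mean as a between-group difference.** Suppose both arms start at 8.95 and acupuncture ends at 6.90 on day 10. The experimental arm would have to reach 6.90 − 2.05 = 4.85, a fall of 8.95 − 4.85 = 4.10 points. That is twice the acupuncture change of 2.05.

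**Power for other true differences.** Two-sample t-test, two-sided 0.05, 19 evaluable per arm, SD 1.93. The differences below 2.05 are illustrations and do not come from the document.

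| True between-group difference (NIHSS points) | Power |
|---|---|
| 2.05 | 89% |
| 1.8 | 80% |
| 1.5 | 64% |
| 1.26 | 50% |
| 1.0 | 34% |
| 0.5 | 12% |

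The difference detectable with 90% power is 2.09 points, and with 80% power 1.80. If all 21 per arm are evaluable, power at 1.0 point is still 37%. A normal approximation gives slightly higher values (91% at 2.05, 67% at 1.5, 36% at 1.0).

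**Type of test.** Section 2.13.1 assigns NIHSS to a rank sum or χ² test. With the normal-theory efficiency of 0.955, the rank sum test gives about 87% instead of 89% at 2.05 points. For χ² no figure can be given, because no categories are stated.

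**Standard deviation.** The 1.93 stands beside the pre-treatment mean. The SD of the day-10 score, or of the change, is not given. Power for 2.05 points at assumed SDs:

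| Assumed SD | Power for 2.05 points |
|---|---|
| 1.5 | 98% |
| 1.93 | 89% |
| 2.5 | 69% |
| 3.0 | 54% |

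**Precision.** Half-width of the 95% confidence interval for the difference, with 36 degrees of freedom: 2.028 × 1.93 × √(2/19) = 1.27 points.

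**Could it be a paired calculation?** A paired before-after calculation would use the SD of the change, without the factor 2, and would not then be doubled for two groups. Section 2.11 has the factor 2 and doubles n. The paired reading does not fit.

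**The case against.** The best defence is that the study is described as preliminary in section 2.11 and as a pilot in the Discussion, which also admits the small sample. A pilot need not be powered for its comparison, and the fix leaves the number of patients and the analysis unchanged. This stands as mitigation. It does not remove the fault, because section 2.11 justifies 42 formally with α and β, section 2.13.1 plans between-group tests, and the Discussion says the trial will prove the treatment effective.

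Several stronger readings are tempting, and the document does not support them:

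- **That the sample size is miscalculated.** It is not; 19 and 42 both follow from the inputs. The fault lies in what the difference represents.
- **That the protocol claims 90% power, or passes the two means off as those of the two arms.** It gives only β = 0.1, and it labels both means as the acupuncture group's.
- **That any advantage below 2.05 points would probably be missed.** Power stays above 50% down to about 1.26 points, so at SD 1.93 a non-significant result is the likelier outcome only below that.
- **That the protocol's own rationale predicts a small difference.** The Introduction likens acupoint magnetic stimulation to acupuncture, but the experimental arm adds M1 stimulation, and the same section says central and peripheral effects superimpose. Some advantage is plausible; its size is not given.
- **That the day-10 SD must exceed 1.93.** The eligibility range of NIHSS 4 to 15 does not establish this, and an SD of change could be smaller.
- **That non-significance will be reported as equivalence.** No section proposes it.

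**Conclusion.** The point holds. The effect entered in section 2.11 is a within-arm change, so the 90% power implied by β = 0.1 does not apply to the comparison in section 2.13.1 unless the experimental arm improves by about 4.1 points. The document gives no support for that.

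No single corrected sample size can be derived, because no experimental-arm mean or expected between-group difference is stated. For the same reason the documents do not show that 42 is too few; they show that the power is unknown and that its stated basis does not address the question. How much this matters depends on the true difference: little near 2 points, a great deal at 1 point or below. The power figures assume 19 evaluable per arm, a common SD of 1.93, approximately normal scores and a t-test. Among these the SD is the least secure.

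**What to change.** Keep 42 and rewrite section 2.11 so that the acupuncture before-after change no longer serves as the between-group difference. Suggested content:

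- With 19 evaluable patients per arm, an assumed common SD of 1.93 and a two-sided 0.05 t-test, power is about 90% only for a between-group day-10 NIHSS difference of about 2.1 points. It is 80% for 1.8, 64% for 1.5, 50% for about 1.26 and 34% for 1.0. It is slightly less if the rank sum test is used.
- The SD of 1.93 comes from the pre-treatment score. The SD of the day-10 score or of the change is not known. Power for 2.05 points ranges from about 98% at an assumed SD of 1.5 to 54% at 3.0.
- 42 is a pilot size. It should not be called precision-based, because it was not derived from a target interval width.
- The between-group difference will be reported with its 95% confidence interval, whose expected half-width is about 1.3 points at SD 1.93.

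The cost is a rewording of one section and a less favourable statement of power. No patients are added and no test changes.
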